**Study Design**

Each patient will be examined by at least five independent principal investigators. Investigator 1 will perform a basic oral examination using a clinical inspecting apparatus and X-ray, check all of the inclusion and exclusion criteria, and ensure that the informed consents are signed by the patients at the Registration Center. Next, Investigator 2 will perform the pre-surgical treatments, re-check the inclusion and exclusion criteria, and extract the tooth/teeth that will be subjected to cell isolation by Investigator 4. Investigator 2 will select no more than 2 teeth (from different regions) to be investigated in each patient. Following the collection of baseline data from the selected tooth/teeth by Investigator 3, Investigator 4 will culture the cells, make the cell products, and create an allocation table consisting of 2 cases per block that will be allocated to the Control group (Bio-oss® only) and Cell group (Bio-oss® and cell sheets). According to this allocation table, a label indicating the corresponding group will be attached to each tooth; thus, each tooth will be randomly assigned to one of the two treatment groups. The maximum number of teeth from one patient will be 2. Hence, if one tooth is allocated to the Control group, the other will be automatically assigned to the Cell group. However, if a patient only has one tooth chosen for investigation, it has a fair chance of being allocated to either group. Once a tooth is assigned to a group, it will be kept in a secure locked drawer inaccessible to all other study personnel. All of the patients will receive oral hygiene instructions, a tooth cleaning and basic dental therapies if needed, such as cavity filling and occlusal adjustment. The periodontal surgery will be performed 4-5 weeks after these pre-surgical treatments. When the oral condition and cell products are both ready for surgery, Investigator 4 will be asked to give the assigned implants (Bio-oss® only or a combination of Bio-oss® and cell sheets) to the physician (Investigator 5), who will then perform the surgery. This procedure ensures that the randomization is not influenced by the physicians taking part in this study. Investigator 4 will record the patients’ details and number the envelope assigned to each tooth. Investigator 3 will perform the follow-up study (data collection, safety assessment, etc.) of the patient, and the blind will not be broken until this clinical trial is completed.

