**Patients and enrolment**

Patients with periodontitis visiting our dental institution will be requested to participate. This study will be conducted in compliance with Good Clinical Practice guidelines. Prospective patients who provide written informed consent will undergo clinical inspection and an oral cavity diagnosis. We will then select approximately 30 patients (approximately 40 testing teeth) who satisfy the selection and exclusion criteria described below (most of these criteria were chosen from previous similar periodontal clinical trials [34,35]).

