**Statistics**

This study will be performed using a per-protocol analysis. In this analysis, all of the randomized teeth will receive at least one therapy, but teeth that do not receive treatment will be excluded (modified per-protocol analysis). The last-observation-carried-forward method will be used for the per-protocol analysis. The missing data points will be input into the post-baseline follow-up visits from the last observation available for each patient. For analysis, we will use SAS version 8.2 software (SAS Institute Inc., Cary, North Carolina, USA). The per-protocol set analysis will be performed for the primary outcome. The baseline between-group comparisons within age and clinical examination indices will be performed using independent group *t* tests. The between-group comparison of sex will be performed using Fisher’s exact probability test. The changes in clinical examination indices will be tested using a repeated-measures analysis of variance. The level of statistical significance will be set at *p*<0.05.

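### Two-tooth patients contribute one tooth to each arm, but no analysis named in the Statistics section fits this mix of paired and single teeth; the likely cost is lost precision, not false positives

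*Protocol*

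**What the plan says.** The Study Design section of the protocol makes the tooth the unit of randomisation: "each tooth will be randomly assigned to one of the two treatment groups". It limits each patient to two teeth ("The maximum number of teeth from one patient will be 2") and ties the second to the first: "Hence, if one tooth is allocated to the Control group, the other will be automatically assigned to the Cell group". A patient with a single study tooth is allocated in parallel: "if a patient only has one tooth chosen for investigation, it has a fair chance of being allocated to either group". The Patients and enrolment section plans "approximately 30 patients (approximately 40 testing teeth").

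The Statistics section defines its analysis set by teeth and names three tests. For baseline, "The baseline between-group comparisons within age and clinical examination indices will be performed using independent group" t tests, with Fisher's exact test for sex. For outcomes, "The changes in clinical examination indices will be tested using a repeated-measures analysis of variance". It names no subject, no repeated factor, no patient term and no paired or clustered method. Significance is set at 0.05.

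Under Efficacy assessment, alveolar bone height (primary) is assessed at 3, 6 and 12 months. CAL, PD and GR are recorded at baseline and 12 months.

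**The concern.** The allocation rule produces two kinds of data: pairs of teeth in one mouth, one per arm, and single teeth in a parallel comparison. An analysis has to recognise both, and none of the three named tests does.

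Age and sex belong to the patient, so a test between tooth groups enters each two-tooth patient on both sides. That is wrong whatever the correlation.

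For the treatment comparison, two teeth in one mouth share hygiene, healing and other patient factors, so their outcomes are likely to be positively correlated. Treating them as independent gives the wrong standard error. With only about 40 teeth and an aim of showing that cells add to the graft alone, lost precision can turn a real benefit into a null result. Intervals that are too wide also misinform the later trials that the Discussion expects this one to guide.

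**Working it through.** The protocol gives no standard deviation, effect size, correlation or power, so there is no stated figure to reproduce.

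**Inputs from the protocol.** About 30 patients and 40 teeth; at most two teeth per patient; two-tooth patients split across arms; significance level 0.05.

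**Assumptions.** Exactly 30 and 40; single teeth split 10 and 10; equal SD of 1 in both arms; two-sided test; within-patient correlation rho from 0 to 0.7.

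**1. Number of pairs.** With x two-tooth patients, 30 + x = 40, so x = 10. That leaves 20 one-tooth patients, and each arm has 10 + 10 = 20 teeth.

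**2. Variance if teeth are taken as independent.** 2/20 = 0.100, so SE = 0.316.

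**3. True variance of the same difference.** Each pair puts one tooth in each arm, so its covariance is subtracted: 0.100 - 2 x 10 x rho/20² = 0.100 x (1 - rho/2). At rho = 0.5 this is 0.075, so SE = 0.274.

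**4. Consequence for the test.** The SE is too large by 1/sqrt(1 - rho/2). The actual type I error is 2 x [1 - Phi(1.96/sqrt(1 - rho/2))].

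**5. Variance when the pairing is used.** Weighting pairs and singles by inverse variance gives 1/[10/(2(1 - rho)) + 10/2]. At rho = 0.5 this is 1/(10 + 5) = 0.067, so SE = 0.258. This treats rho as known, so it is a best case.

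| rho | SE, independent teeth | true SE | ratio | type I error, formula | type I error, simulated t test | SE using pairs (best case) |
|---|---|---|---|---|---|---|
| 0 | 0.316 | 0.316 | 1.00 | 5.0% | 5.1% | 0.316 |
| 0.2 | 0.316 | 0.300 | 1.05 | 3.9% | 3.8-4.0% | 0.298 |
| 0.5 | 0.316 | 0.274 | 1.15 | 2.4% | 2.5-2.6% | 0.258 |
| 0.7 | 0.316 | 0.255 | 1.24 | 1.5% | 1.5-1.6% | 0.215 |

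At rho = 0.5, the difference detectable with 80% power, (1.96 + 0.84) x SE, is 0.89 SD for independent teeth and at best 0.72 SD with the pairing used.

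**6. Sensitivity to the approximate enrolment figures.** With 40 teeth, 32 patients give 8 pairs and 28 give 12. At rho = 0.5 the true variance is then 0.100 - 2 x 8 x 0.5/400 = 0.080 or 0.100 - 2 x 12 x 0.5/400 = 0.070. Type I error is about 2.8% or 1.9%.

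**7. The two classical readings of the repeated-measures ANOVA.**
- Tooth as subject, visit repeated: all 40 teeth are used, but 20 of them are paired and the pairing is ignored, as in steps 2 to 4.
- Patient as subject, treatment within patient: only about 10 patients have both conditions, so about 20 of 30 drop out.

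**8. Check on the obvious replacement.** A REML model with a random patient effect was simulated under no treatment effect, with one value per tooth, 10 pairs and 10 + 10 singles (20,000 runs), using fixed degrees of freedom and no small-sample correction. At rho = 0.5 and 0.2 it rejected 7.2% and 6.6% of the time with 38 df, and 6.9% and 6.4% with 28 df. A patient effect alone would therefore swap a conservative test for a liberal one.

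**The case against.** The strongest reply is that the protocol does not say the ANOVA treats teeth as independent. It leaves the unit unnamed, and a patient term is the kind of detail a statistical analysis plan may hold. This stands in part: independence is explicit only for the baseline tests, which do not enter the treatment effect, and is an inference for the ANOVA. It does not dispose of the point, because neither classical reading of the named method fits the allocation rule. A later plan would have to depart from the section or add to it.

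The size is also open. No correlation is given, and the Study Design section asks for a patient's two teeth to come from different regions, so a low value is possible. At 0.2 the SE is only 5% too large, and at 0 nothing is lost.

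A reader might infer two stronger things. One is that ignoring the clustering inflates false positives, as it often does. Here it does not: paired teeth are always in opposite arms, so positive correlation makes the independent-teeth test conservative and leaves the difference in means unbiased. The other is that the split was chosen to gain precision and the analysis defeats that purpose. The protocol gives no such rationale.

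**Conclusion.** The point holds at moderate severity. The Statistics section names no analysis that suits about 10 within-patient pairs plus about 20 single teeth, and its baseline tests of age and sex count two-tooth patients twice. If outcomes are analysed with teeth as independent units, the SE of the group difference is overstated by 0% to 24% for correlations of 0 to 0.7. Nominal 5% tests then run at about 5% (rho 0), 3.8% (0.2), 2.5% (0.5) and 1.6% (0.7). The loss is in precision and power.

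These figures are a range, not an estimate. They rest on the assumed correlation, the enrolment numbers taken as exact, equal variances and a two-sided test. That the ANOVA ignores pairing is the likelier reading, not a stated fact.

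**What to change.** In the Statistics section:

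- **Alveolar bone height.** Replace the ANOVA with a linear mixed model on all treated teeth. Fixed effects: group, visit (3, 6 and 12 months), group by visit, and baseline bone-defect depth. Random effects: patient, and tooth within patient. Name the Kenward-Roger correction of standard errors and degrees of freedom; without a correction the test rejects about 7% of the time under the null. The size of the corrected test was not simulated here and should be confirmed for this layout.
- **CAL, PD and GR.** Only one post-baseline visit exists, so a visit term and a tooth effect cannot be estimated from one change per tooth. Use the 12-month change per tooth, with group and the baseline value as fixed effects, a random patient effect and the same correction.
- **Age and sex.** Describe them per patient in three sets (one tooth in Cell, one tooth in Control, two teeth), without between-group tests.

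The cost is revised wording and slightly more programming, with no new data. If the correlation is near zero, a few degrees of freedom are given up for little return. This change does not settle which visit carries the primary comparison.

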**Fourth Military Medical University**

**2011.06**

**Abstract**

**Background**: Periodontitis, which progressively destroys tooth-supporting structures, is one of the most widespread infectious diseases and the leading cause of tooth loss in adults. Evidence from animal studies indicates that stem cells derived from either bone marrow or the periodontal ligament (PDL) can be used in therapies for the regeneration of lost or damaged periodontal tissues. The aim of this clinical trial is to identify the safety of the clinical use of stem cells in periodontal therapy and to verify whether stem cells in combination with Bio-oss® are more effective than Bio-oss® alone in guided tissue regeneration (GTR) techniques for treating periodontal disease in human patients.

**Methods/Design**: In this protocol, we designed a single-center randomized trial to treat periodontal disease using GTR techniques and bovine-derived bone mineral (BDBM, Bio-oss®) with or without the incorporation of autologous periodontal ligament stem cells (PDLSCs). In total, approximately 30 periodontitis patients aged 18 to 65 years with a total of approximately 40 test teeth with periodontal intrabony defects and who satisfy our selection and exclusion criteria will be enrolled. These patients will be randomly assigned to either the Cell testing group (treatment with GTR and PDLSC sheets in combination with Bio-oss®) or the Control group (treatment with GTR and Bio-oss® without containing cells). During a 12-month follow-up, we will examine the extent of any adverse events related to the use of PDL cells. Moreover, the primary outcome is the magnitude of change in the alveolar bone height, and the secondary outcome measures are improvements in clinical attachment level (CAL), probing depth (PD), and gingival recession (GR).

**Discussion**: The results of this trial will assess the efficacy, safety and feasibility of using autologous PDLSCs to treat periodontal intrabony defects, and these data will provide primary clinical evidence for the future use of autologous stem cells in regenerative periodontal therapy.

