***Inclusion criteria***

- those 18 years old and <65 years old;
- those diagnosed with a 2- or 3-walled vertical intrabony defect 3 mm deep from the top of the remaining alveolar bone from radiography and clinical periodontal parameters;
- those who have accomplished the initial preparation and shown good compliance;
- those with a mobility of Degree 2 or less for the tooth under investigation and with a width of the attached gingiva for which the existing GTR and bone graft implantation treatments are considered appropriate;
- those for whom supportive periodontal treatment is applicable (the tooth has the potential to be maintained for at least 3 years) and in accordance with the usual post-operative procedures following flap operation and GTR treatment;
- those whose oral hygiene is well established and who are able to perform appropriate tooth brushing and cleaning following instructions from the investigators and/or sub-investigators after investigational drug administration;
- those who have at least one tooth (e.g., wisdom tooth) that needs to be extracted due to impacted or non-functional reasons and who agree to the tooth extraction;
- those who understand the purposes of the trial and are capable of making an independent decision to comply with trial requirements.

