Our geometrically standardized radiography employs dental film (Kodak InSight Super Poly-Soft; Eastman Kodak Company, New York, USA) and photograph indicators (Cone Indicator-II; Hanshin Technical Laboratory, Hyogo, Japan) that are customized with resin stents. Two doctors specializing in dental radiology from the Department of Oral Diagnosis at Fourth Military Medical University School of Stomatology will measure the changes in the alveolar bone height (%) using the methods described below (Figure 2). Each examiner blinded to the treatment conditions will independently measure this value, and the median of 2 measurements taken from the same image will be selected for analysis. In addition, a dental CT that reports data automatically will be used to assess bone regeneration in selected cases. These data will be used for information purposes only or as a reference for the design of subsequent trials (not included in the analysis of this trial).

[figure not shown]

**Figure 2**. Schematic illustration of the bone regeneration assessment using standardized radiography. Points C, A and B represent the cementoenamel junction, apex and bottom of the bone defect, respectively. The examiner measured the tooth axis heights between Points C and A and between Points C and B (bone-defect depth, BDD) on the X-ray for each patient. To adjust for slight errors due to imaging, the measurements from 5 examiners were multiplied by the A-C ratio of the before to after administration to correct for C-B after administration. Based on C-B data before surgery and during follow-up (3, 6 and 12 months), increse of BDD was calculated to serve as an indicator of increase in alveolar bone height post-operation [37,38].

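### The analysis of outcome changes names no baseline covariate, although each tooth's pre-surgical value is collected; adding it as a covariate would be a free gain in precision

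*Protocol*

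**What the plan says.** The Statistics section names one method for outcomes: "The changes in clinical examination indices will be tested using a repeated-measures analysis of variance". It lists no covariate. Its only other use of baseline data is between-group testing: "The baseline between-group comparisons within age and clinical examination indices will be performed using independent group" t tests, with Fisher's exact test for sex.

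Baseline values exist for every outcome. The Figure 2 legend derives bone gain from the pre-surgical distance: "Based on C-B data before surgery and during follow-up (3, 6 and 12 months"). The Efficacy assessment section has CAL, PD and GR recorded at baseline and at 12 months.

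Teeth are not uniform at entry. The inclusion criteria admit a "2- or 3-walled vertical intrabony defect" and give an entry depth with no upper limit. The Study Design section has an investigator "create an allocation table consisting of 2 cases per block" and mentions no stratification by depth or wall number. For a patient with two study teeth, "if one tooth is allocated to the Control group, the other will be automatically assigned to the Cell group". The trial is small: "We will then select approximately 30 patients (approximately 40 testing teeth").

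**The concern.** A change score subtracts the baseline value with a fixed coefficient of one. Unless baseline and follow-up are almost perfectly correlated, that removes too much. The change is then correlated with the starting value, and a group that happens to start with deeper defects tends to show more apparent gain whatever the treatment does. Regression on baseline estimates the coefficient instead of fixing it. It removes that conditional shift and usually narrows the interval.

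This matters more in a trial of about 40 teeth than in a large one, because chance imbalances are larger and precision is scarce. The planned baseline t tests do not fill the gap: they alter no treatment estimate, and a sizeable imbalance can be non-significant.

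**Working it through.** The protocol gives no power calculation, effect size, SD or baseline/follow-up correlation, so there is no stated figure to reproduce. What follows is an illustration under declared assumptions.

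**Inputs from the protocol.** About 40 teeth in about 30 patients (Abstract; Patients and enrolment). Allocation in blocks of two gives about n = 20 teeth per group. If no patient has more than two teeth, 40 − 30 = 10 patients contribute two teeth and 20 contribute one. The significance level is 0.05.

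**Assumptions.** Two-sided testing; the same SD at baseline and follow-up (the unit below); raw change at a single follow-up; independent teeth; correlation rho from 0.3 to 0.9.

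**Chance imbalance.** The SE of the baseline mean difference is sqrt(2/20) = 0.316 SD. The chance of an absolute difference above 0.5 SD is P(|Z| > 0.5/0.316) = P(|Z| > 1.58) = 0.11; above 0.3 SD it is 0.34. An observed gap of exactly 0.5 SD gives t = 1.58, p about 0.12, so the planned baseline test would not flag it.

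**Shift caused by an imbalance.** If the groups differ by 0.5 SD at baseline, the expected follow-up difference without any treatment effect is 0.5 × rho. The difference in change is therefore off by 0.5 × (1 − rho) SD.

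**Variance.** Per tooth, the change score has variance 2(1 − rho) and the baseline-adjusted outcome 1 − rho². The ratio is (1 + rho)/2. Estimating the slope costs a factor of about 1 + 1/(2n − 4) = 1 + 1/36 = 1.028.

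| rho | (1 + rho)/2 | with slope cost | variance cut | 20 adjusted teeth per group act like | shift from 0.5 SD imbalance |
|---|---|---|---|---|---|
| 0.3 | 0.65 | 0.67 | 33% | 30 | 0.35 SD |
| 0.5 | 0.75 | 0.77 | 23% | 26 | 0.25 SD |
| 0.7 | 0.85 | 0.87 | 13% | 23 | 0.15 SD |
| 0.9 | 0.95 | 0.98 | 2% | 20.5 | 0.05 SD |

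A simulation of 20,000 trials gave ratios of 0.768 at rho 0.5 and 0.873 at rho 0.7, which agrees with the table.

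**Power.** Take the effect that the adjusted analysis detects with 80% power (normal approximation, before the slope cost). The unadjusted change analysis has 62%, 68%, 73% and 78% power for that effect at rho 0.3, 0.5, 0.7 and 0.9.

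**Three visits instead of one.** Suppose the mean of the three follow-ups is compared and all pairs of measurements share the same rho. The mean has variance v = (1 + 2rho)/3. The ratio is then (v − rho²)/(v + 1 − 2rho) = 0.475, 0.625, 0.775 and 0.925 at the same four values, before the slope cost. Under this simple pattern the single-visit figures do not overstate the gain.

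**The case against.** Five objections deserve an answer.

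- **Covariates belong in the SAP.** The Statistics section is short and does not forbid a covariate; an unseen SAP may add one. That is fair, and it is why this is an improvement and not an error. The protocol does, however, commit to a named test for outcomes and to named baseline tests, and a better choice is available for the first.
- **The sentence names clinical examination indices, not radiographic bone height.** This stands as a caveat. Applying it to the primary outcome is an inference: it is the only outcome test given, and bone height is the outcome followed at 3, 6 and 12 months. If the inference is wrong, the point still applies to CAL, PD and GR, and the primary outcome has no named test.
- **Baseline is already handled.** A reader might infer that baseline enters only through significance tests. It does not: the outcomes are changes, so baseline is subtracted. What is missing is regression adjustment.
- **The figures are generic.** This stands. The radiography section expresses bone change as a percentage and the Efficacy assessment section as a rate of increase; for a percentage of baseline, the variance ratio and the shift do not carry over as written. The figures also ignore that about 10 patients have one tooth in each group. That pairing balances patient-level factors, though not the depth of each tooth's defect. C-B is the same distance on the same tooth, taken with stents and corrected for imaging error, so a high rho and a small gain cannot be ruled out.
- **The protocol attaches no rule to the baseline tests.** A reader might infer that their p-values decide whether to adjust, or certify balance. The protocol says neither.

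**Conclusion.** The point holds as an available improvement in efficiency. The plan compares changes without a baseline covariate although the covariate is already measured. Under the stated assumptions, adjustment cuts the variance of the group difference by between about 33% (rho 0.3) and 2% (rho 0.9). It also removes a shift of 0.35 to 0.05 SD when a 0.5 SD imbalance has occurred. The correlation is not documented, so the position within those ranges is unknown.

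A stronger reading, that the planned comparison is biased or invalid, is not supported. Over randomisation the comparison of changes is unbiased and its standard error already allows for chance imbalance. The bias described here is conditional on an imbalance having arisen.

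**What to change.** In the Statistics section, state that change in alveolar bone height, and in CAL, PD and GR, will be analysed with the tooth's own pre-surgical value of that measure as a prespecified covariate, in a model that accounts for two teeth from one patient. For bone height the covariate is pre-surgical C-B. Say explicitly that this sentence covers the primary outcome. The outcome variable need not change: for a raw change, regressing the change on baseline gives the same treatment effect as regressing the follow-up value on baseline.

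Number of defect walls (2 or 3) is an optional further covariate; nothing in the protocol allows its benefit to be sized.

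Replace the baseline t tests and Fisher's exact test with a descriptive table by group.

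The cost is a sentence or two of wording and one model degree of freedom per covariate. No extra patient, visit or measurement is needed.
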